### Food samples

In contrast to pure tastes commonly used in research on gustatory perception, four ordinary, more ecologically valid mixtures of chocolate ice cream containing low vs. high levels of fatness and low vs. high levels of sweetness (Table 5) will be presented in 100-ml disposable Styrofoam cups at room temperature and in counterbalanced order across participants. Chocolate ice cream was selected according to the assumptions that chocolate ice cream is likely to be a forbidden food for AN and BN participants, and that AN participants can be expected to have strong aversive associations. The samples are stored at minus 18°C. Optimal mixtures were elaborated at the School of Agricultural, Forest and Food Sciences (Department of Food Science & Management; Bern University of Applied Sciences) and obtained considering previous studies on taste sensory and hedonic ratings (Sunday and Halmi, 1990) and surface response method (Drewnowski et al., 1987b) in AN and BN. Assuming an all-or-nothing (i.e., dichotomous) approach to food in AN and BN, regardless of the fat or sucrose levels, the specific ingredients of the samples were further selected in order to increase differences across ice cream samples in terms of sweetness, creaminess, expectation of caloric content and hedonic reactions (Table 6). In this sense, although previous studies have found pronounced aversion to the sugar-fat mixtures in AN patients, variability in aversive scores across combinations of sweet taste and fat together has also been demonstrated. For instance, differences comparing liking response profiles as a function of increasing sucrose content (0–20% wt/wt) separately from different fat samples (0.1–52.7% fat wt/wt) have been observed in AN (restrictive) and bulimic patients, and in both currently-ill and recovered patients (e.g., Drewnowski et al., 1987b; Sunday and Halmi, 1990). Finally, while water will be used as control stimulus, two savory (high-fat and low-fat) sauces will be added in study 2 as additional comparators to demonstrate that any differences detected are unique to sweet-fat foods in BN patients as previous research suggests.

**Table 5 T5:** Characterization of the food samples with low and high content of fatness and sweetness.

**Components**	**Low fatness and low sweetness**	**Low fatness and high sweetness**	**High fatness and low sweetness**	**High fatness and high sweetness**
Dry matter (%)	30.0	30.0	39.5	39.5
Fat content (%)	1.2	1.2	11.4	11.4
Carbohydrate (g)	21.8	21.8	22.1	22.1
Protein (g)	4.7	4.8	4.8	4.8
Fat (g)	1.2	1.2	11.9	11.9
Kcal total	117.0	117.3	215.1	215.4
Kcal (%)	54.3	54.4	99.9	Reference = 100
Relative sweetness	14.45	28.01	14.76	28.8
**INGREDIENTS (%)**				
Whole milk	0.0	0.0	35.0	35.0
Skimmed milk	45.6	45.6	0.0	0.0
Cream	0.0	0.0	27.2	27.2
Water	27.1	27.1	11.0	11.0
Skimmed milk powder	7.6	7.6	4.2	4.2
Sucrose	8.7	8.7	6.8	6.8
Dextrose	4.3	4.3	4.5	4.5
Glucose DE 35–40%	2.2	2.2	1.5	1.5
Sweetener (Aspartam)	0.0	0.1	0.0	0.1
Stabilisator/emulfiser	0.8	0.8	0.7	0.7
Chocolate powder	0.9	0.9	0.8	0.8
Cocoa powder	2.8	2.8	2.6	2.6
Color (E150d)	0.6	0.6	2.0	2.0
Flavor	0.1	0.1	0.1	0.1
Polydextrose	0.0	0.0	4.5	4.5
Whey powder	0.0	0.0	2.0	2.0

*The high fatness and high sweetness is the food sample reference for kcal*.

**Table 6 T6:** Preliminary sensory testing results (*N* = 5; normal weight individuals) for the food samples with low and high content of fatness and sweetness.

**Attribute**	**Food sample**			
	**Low fatness and low sweetness**	**Low fatness and high sweetness**	**High fatness and low sweetness**	**High fatness and high sweetness**
Sweetness	2.75	5.96	3.50	6.25
Creaminess	2.17	3.42	4.96	5.50
Chocolate flavor	4.08	4.58	4.17	4.63
Caloric content	3.00	5.83	5.21	6.50

*The attributes were rated in a scale from 1 (not sweet, not creamy, too week, very low) to 7 (very sweet, vey creamy, too intensive, very hing)*.

### Outcome measures

Information about the primary and additional secondary outcome measures and instruments is summarized in Table 2.

### Study design

The present international and multi-center research uses a quasi-experimental, cross-sectional design with concurrent controls aims at comparing gustatory perception and hedonics of taste among six groups of participants: R-AN, C-AN, U-CT, N-CT, R-BN, and C-BN, under two counterbalanced conditions of testing: sip-and-spit vs. swallow test condition. The use of a rigorous quasi-experimental design with a well-established type of psychopathology represents an important approach in the experimental psychopathology literature (Zvolensky et al., 2013), particularly in the context of eating disorders for both ethical and pragmatic reasons. However, the limitations are related to the lack of random assignment into groups, which leads to non-equal test groups, which can limit the generalizability of the results to a larger population. In order to reduce the impact of this limitation, threats to validity will be minimized controlling the following factors: comorbidity, stage-of-illness, age-at-onset, duration of illness and time in treatment, depressive mood, craving for food, biased cognitions about weight, current hunger, thirst and food familiarity. In addition, age-matched and weight-matched controls (to the extent possible) will be included in the research design to increase the chances of finding differences between groups. Additional controls by limiting our inclusion criteria are not envisaged as this would make it even more difficult to obtain samples of adequate size (therefore reducing statistical power) and limiting the generalizability (and hence the external validity) of the study protocol.

### Statistical and analytic plan

#### Sample size calculation

Sample size calculations were based on findings of small to medium effects on eating behavior in patients with anorexia and bulimia by our group (e.g., Munsch, 2014) using the software G^*^Power (version 3.13). Assuming two-sided tests with Alpha = 0.05, Beta = 0.2, and effect size *f* = 0.20, the required sample size would be 80 to ensure a power >0.80 in each one of the two studies with a sample distribution of N_C−AN_ = 15, N_C−BN_ = 15, N_R−AN_ = 10, N_R−BN_ = 10, N_U−CT_ = 15, and N_N−CT_ = 15. To obtain the required number of 50 patients per study and taking into account a participation rate of 80% and a dropout rate of 20% in the patient population, a total of 60 patients per study will be needed. Based on our recruitment and testing experiences in Switzerland and Luxembourg (average annual recruitment of 35–40 AN and 35–40 BN patients), the access to a sufficiently powered sample of patients seems to be guaranteed. Finally, in order to achieve the sample size suggested by the power analysis, a sample of 30 healthy controls (university students) per study will be recruited in Fribourg.

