## Methods

### Participants

A total sample of 160 female participants will be recruited in Switzerland and Luxembourg. AN (restricting-type), BN (without history of AN) patients meeting DSM-5 (American Psychiatric Association, 2013) criteria will be divided into currently-ill (C) and recovered (R). Thus, C-AN (*n* = 30) and C-BN (*n* = 30) will be compared to R-AN (*n* = 20) and R-BN (*n* = 20) patients, as well as to two age-matched control (CT) groups: underweight (U-CT; *n* = 30) and normal-weight (N-CT; *n* = 30) without eating disorders. BN with previous history of AN or binge-eating/purging type of AN will be excluded to enable a better differentiation between these disorders. Participants will be asked to provide demographic information, height, weight, duration of illness, time in treatment, age at onset, duration of recovery where applicable, and self-reported salivary, metabolic, and/or otorhinolaryngologic disorders. Ethical permission was obtained from Swiss Ethics Committee and from the Ethics Review Panel of the University of Luxembourg. Participants will provide written informed consent.

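### The 60 patients per study do not yield the required 50 at the stated participation and dropout rates, and the recruitment total of 160 disagrees with that figure

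*Protocol article*

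**What the plan says.** Under Sample size calculation, the protocol article sets its inputs as "Assuming two-sided tests with Alpha = 0.05, Beta = 0.2, and effect size *f* = 0.20" and concludes that "the required sample size would be 80 to ensure a power >0.80 in each one of the two studies". The 80 are split into 15 C-AN, 15 C-BN, 10 R-AN, 10 R-BN, 15 U-CT and 15 N-CT, which is 50 patients and 30 controls.

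The patient number is then inflated. The target is stated as "To obtain the required number of 50 patients per study", and the losses and the result are given as "a participation rate of 80% and a dropout rate of 20% in the patient population, a total of 60 patients per study". Thirty healthy controls per study are added without inflation.

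Under Participants, the article states: "A total sample of 160 female participants will be recruited in Switzerland and Luxembourg". The groups listed there are 30, 30, 20 and 20 patients and two control groups of 30.

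**The concern.** The inflation step names its three inputs (50 required, 80% participation, 20% dropout) and its result (60), so it can be checked directly, and the result does not follow. Separately, the two sections that give recruitment numbers do not agree: one carries an allowance for loss and the other equals the analysis number.

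What is at stake is whether the number at which recruitment stops delivers the 50 patients and 80 participants per study on which the power statement rests. The recovered groups are the most exposed. They are planned at only 10 each per study, and all three hypotheses use recovered participants as comparators.

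**Working it through.** **Inputs**

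- Sample size calculation: 50 patients required per study; 80% participation; 20% dropout; 60 stated as needed; 30 controls per study; 80 analysed per study; f = 0.20; alpha 0.05.
- Participants: 160 recruited, as 30 + 30 + 20 + 20 = 100 patients and 30 + 30 = 60 controls.
- Procedure: each experimental session contains either the study 1 task or the study 2 task. The two samples therefore add, consistent with 160 = 2 × 80.

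**Reproducing the stated 60**

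| Calculation | Result |
|---|---|
| 50 × 1.2 | 60 |
| 50 / 0.8 (one 20% loss) | 62.5, so 63 |
| 50 / (0.8 × 0.8) (both losses) | 78.1, so 79 |
| 50 × 1.2 / 0.8 | 75 |
| 50 × 1.2 × 1.2 | 72 |
| 50 × 1.4 | 70 |
| 50 / 0.6 | 83.3, so 84 |

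Only the first line gives 60. It adds 20% of the target where the target should be divided by 0.8, and it uses only one of the two rates named.

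**Yield of 60**

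- If 60 are enrolled: 60 × 0.8 = 48 patients, so 48 + 30 = 78 participants per study.
- If 60 are approached and both losses apply: 60 × 0.8 × 0.8 = 38.4 patients, so about 68 participants per study.

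Both fall short of 50 patients. The shortfall is 2 patients per study on the first reading and about 12 on the second.

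**Correct numbers per study**

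- Enrolled: 63, or 64 if each group is rounded up separately (15/0.8 gives 19, 10/0.8 gives 13; 19 + 19 + 13 + 13 = 64).
- Approached, with both losses: 79, or 80 by group (24 + 24 + 16 + 16).

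**The two totals**

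- Participants section: 160 = 2 × (50 + 30), with no inflation in it.
- Sample size section: 2 × (60 + 30) = 180.
- If 160 is the number recruited, 50 patients enter each study. With 20% dropout, 50 × 0.8 = 40 remain, and 40 + 30 = 70 per study. A recovered group of 10 falls to about 8.

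**What this means for power**

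The article does not say which effect was powered, over how many measurements, or with what correlation between them. As an illustration only, take a group × condition interaction with six groups, two conditions and f = 0.20. The noncentrality is f² × N × 2 / (1 − correlation), on 5 and N − 6 degrees of freedom.

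| Assumed correlation | Power at N = 70 | Power at N = 80 |
|---|---|---|
| 0 | 0.37 | 0.43 |
| 0.5 | 0.69 | 0.76 |
| 0.6 | 0.80 | 0.86 |
| 0.7 | 0.91 | 0.95 |

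For a group × food sample interaction (four levels, correlation 0.5) the figures are 0.85 and 0.91. Going from 80 to 70 costs about 0.04 to 0.07 across these cases. The level itself cannot be fixed from the document.

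**The case against.** The strongest reply is that 160 is the evaluable target. The groups under Participants are exactly double the analysis distribution, and the allowance for loss appears separately in the sample size section. On that reading 160 analysed and 60 patients needed per study are compatible, and the 70-per-study scenario would apply dropout to a figure already net of it. This is a fair possibility, but the text says recruited, so the meaning has to be stated. It also does not rescue the 60, which is too small for 50 on any correct reading.

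Second, the shortfall may be small. If participation and dropout describe one 20% loss, or if 60 are enrolled, the right number is 63 and the deficit is two completers per study. This stands, and it limits the severity.

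Third, each participant attends one experimental session of about 1.5 hours in a cross-sectional design, so a dropout could be replaced while recruitment is open. The stated annual recruitment of 35–40 AN and 35–40 BN patients also suggests that more could be reached. That bears on feasibility. It does not correct the stated target, and it is not split into currently ill and recovered patients.

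A reader might also infer that the studies are shown to be underpowered, for instance at 0.69 for N = 70. The document does not support that. The assumptions that give 0.69 at N = 70 give 0.76 at N = 80, below the power above 0.80 that the article reports for 80, so they cannot be the ones it used. At a correlation of 0.6, power at N = 70 is still 0.80. Study 1 also compares d′, C and ß by methods other than an ANOVA, so these illustrations do not describe it.

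**Conclusion.** The concern holds as an arithmetic error and an internal inconsistency. The 60 patients per study should be 63 enrolled and, if non-participation is a separate earlier loss, 79 approached. As written, 60 gives 48 or about 38 against the required 50. The total of 160 differs by 20 from the 180 that the sample size section implies. If 160 is the number recruited, it leaves about 70 evaluable per study.

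The size depends on two things the article does not state: whether 60 and 160 count people approached, enrolled or evaluable, and whether the two rates are successive losses. The calculations also assume that loss is confined to patients, as the article does. A reader might conclude that the plan makes no allowance for loss at all, but this goes too far: the sample size section does make one, only too small, and 160 may be meant as the evaluable number. The base figure of 80 is taken as given; it cannot be verified without the software inputs. This should be fixed, but it leaves the design, tests and hypotheses unchanged.

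**What to change.** 1. State whether 60 and 160 are numbers approached, enrolled or evaluable, and whether participation and dropout are two successive losses.
2. Then take one of two routes:
   - Correct the patient number to 63 enrolled and 79 approached per study. With 30 controls per study, the total enrolled is 2 × (63 + 30) = 186.
   - Keep the planned recruitment and restate the expected evaluable number: 48 patients per study from 60 enrolled, or 40 from 50 enrolled. Report power at the resulting 78 or 70 participants, using the sponsor's own G*Power inputs (tested effect, number of measurements, correlation).
3. Make the Participants and Sample size calculation sections give the same total, with the same meaning.

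The second route costs only text and a slightly less favourable stated number or power. The first adds 3 enrolled patients per study to the planned 60, or 13 per study if recruitment would otherwise have stopped at 50.

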#### Data processing

In study 1, three direct measures will be derived from the response data of the 2AFC procedure using the SDT (Hautus et al., 2009): the unaffected sensory sensitivity measure (d′) and the two most popular measures of response bias (C and ß). Specifically, the SDT measures will be calculated following Stanislaw and Todorov's (1999) mathematical formulae, with d′ = [z(H)-z(F)]/√2 and z(H) and z(F) are transformations of the hit and false alarm rates to inverse z-scores; calculated in Excel as DPRIME = NORMSINV(H)-NORMSINV(F). Since the more sensitive is an individual the larger the value of d′, an individual who cannot discriminate levels of sweetness or fatness will have a d′ = 0. By contrast, the measure of response bias based directly on cognitive strategy will be calculated in Excel as C = −(NORMSINV(H)+NORMSINV(F))/2. Response bias measures reflect subject's willingness to report that a sensory attribute is present. For instance, while *C* = 0 refers to an unbiased response, a *C* > 0 indicates that the participant has a conservative response bias (i.e., higher likelihood of responding “The higher level of sweetness/fatness is not present” across all food samples). Conversely, a *C* < 0 indicates the participant has a liberal response bias (i.e., a bias toward responding “The higher level of sweetness/fatness is present” across all food samples). Finally, the second measure of response bias will be calculated in Excel as BETA = EXP((NORMSINV(F)^2^−NORMSINV(H)^2^)/2. Considering ß, the neutral point is ß = 1, while ß > 1 reflects a strict criterion (i.e., tendency to say “absent”) and ß < 1 reflects a lax criterion (i.e., tendency to say “present”).

In study 2, self-reports of pleasure, and facial expression responses will be characterized by a time-intensity (T-I) curve, and its constituent parameters, i.e., maximum intensity reached (Imax; 0–100), time elapsed to maximum intensity (Tmax; in seconds), and area under the curve (AUC; representing the overall emotion of the whole stimuli perceived over the total time of recording). Concerning heart rate variability, interbeat interval data will be exported to Kubios software (University of Eastern Finland, Kuopio, Finland). Inter-beat (R-R) time series will be corrected for artifacts, using a smooth priors de-trending method (λ = 500). Mean heart rate variability in terms of time and frequency domain parameters, mean skin conductance level and mean facial electromyographic amplitudes will determined before tasting food samples at baseline and thereafter.

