	**Ratings**: sweetness and fattiness identity and intensity (score) **SDT parameters**: d′ (sensory sensitiviy), C and ß (response bias based on cognitive strategy)	11-point anchored Likert-type scale (scores from 0 to 10) designed to measure taste perception	Sussex Ingestion Pattern Monitor (SIPM™ 2.0); Sussex University; UK	Primary	Study 1
	**Ratings**: pleasantness of the taste (score)/thirst and hunger level (score)/familiarity of food samples.	Time-intensity measures for pleasure; opportunity to scale the perceived liking dynamically over 60 sec. Labeled magnitude scale for thirst/hunger	SensoMaker™; UFLA, Brazil	Primary/secondary	Study 1 & 2
Behavioural	**Facial expressions**: general emotions, valence and actions units (intensity score)	Positive/negative valence as measure of overall affection; general emotions (joy, anger, surprise, fear, contempt, sadness, disgust); action units as the likelihood of specific facial muscle activations	FACET™ SDK; iMotions Inc., Cambridge Innovation Center, US	Primary	Study 1 & 2
Psycho-physiological	**Cardiovascular**: heart rate and heart rate variability	Cardiovascular Changes as index of cardiac sympathetic activation and autonomic arousal	Module—GSR & Heart Rate and ECG/EMG; Shimmer3 EMG/ECG, GSR Kit and EXG Devices; iMotions Inc., Cambridge Innovation Center, US	Primary	Study 2
	**Electrodermal activity**: skin conductance level (μmhos), skin conductance response rate (count/min)	Changes in the conductivity of skin as index of sympathetic activation		Primary	Study 2
	**Facial electromyography**: EMG powers (mV)	EMG activity of the levator labii (disgust), corrugator supercilia (general negative affect) and zygomatic major (pleasure) muscle regions		Primary	Study 2

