The experimental session will be composed of assessments of thirst and hunger levels, the Thought-Shape Fusion Body State Scale (TSF-B state) and Brief Mood Scale (BMS) questionnaire, a training session to habituate to the testing environment and apparatus, and either the discrimination of two-alternative forced-choice (2AFC) test in study 1 or multiple-sip temporal-liking (MSTL) with taste reactivity (TR) task in study 2. Each experimental session will take around 1.5 h. Concerning the first study (Table 3), the 2AFC test with signal detection theory (SDT) analysis will be used as it provides a high level of power for small food differences and low levels of response bias (Hautus et al., 2009). On the one hand, the 2AFC test is a psychophysical method in which participants are required to select the one of two food samples, which represents the specified attribute best (e.g., the sweeter one). On the other hand, SDT is a sophisticated tool that permits to understand the information processing that takes place in the brain during sensory discrimination testing, providing an accurate index of perceived sensory differences and efficient characterization of cognitive strategy. Therefore, SDT is critical for investigating maladaptive cognitions involved in the processing of received taste information, which affects sensory testing (Smeets et al., 2008). Furthermore, whether and how much gustatory performance depends on low BMI or psychopathology will be examined including under- and normal-weight controls and patients at different stages of the disorder (currently-ill vs. recovered). Finally, in addition to the sip-and-spit condition, a swallow test condition will be included (Eiber et al., 2002) to enhance cognitive bias toward weigh gain underlying the fear of swallowing and quantify the impact of these biased cognitions on gustatory performance. The 2AFC task will be conducted using the SIPM™ software (Sussex Ingestion Pattern Monitoring, version 2.0.11), in which pairs of two samples (with varying levels of sweetness and fatness), presented simultaneously at each trial, are judged in terms of taste identity and intensity (see Table 2).

**Table 3 T3:** Experimental design of the study 1.

**Group**	**Pre-test**	**Test: two-alternative forced-choice task**	
		**Spit condition**	**Swallowed condition**

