R-AN	Training session to habituate to the testing environment	A vs. B, A vs. C, A vs. D, B vs. C, B vs. D, C vs. D	A vs. B, A vs. C, A vs. D, B vs. C, B vs. D, C vs. D
C-AN			
U-CT			
N-CT			
R-BN			
C-BN			

*A, B, C, D, samples of ice cream with a high-/low-sweet and high-/low-fat taste. The order of the paired samples and conditions (swallow and spit) will be randomized. R-AN, recovered anorectic; C-AN, currently ill anorectic; U-CT, underweight control; N-CT, normal weight control; R-BN, recovered bulimic; C-BN, currently ill bulimic. R-AN and R-BN will be assessed at discharge*.

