#### Planned analysis

Analyses will be adjusted for covariates, namely the scores of EDE-Q, BDI-II, FCQ-T-Reduced, TSF-T-Reduced, and hunger and thirst levels. Additional covariates can be added to the model if necessary. In study 1, the procedure for computing the variance of d′, confidence intervals for d', chi-square tests of significance for d′ and comparisons of multiples d′s among groups across two testing conditions will be performed for sweetness, creaminess and caloric content scores according to the Bi et al. (1997) and Bi (2008) approach. Analogous to d′, confidence intervals, hypothesis tests and multiple comparisons for C and ß will be constructed according to Kadlec's (1999) approach.

In study 2, differences in T–I parameters (Imax, Tmax, AUC), self-ratings (hedonic, familiarity) and intensity of facial expressions (emotion, valence and actions units), as well as the cardiovascular, electrodermal and facial electromyographic outcomes, will be analyzed using mixed, three-way factorial ANOVAs with group (six levels) as between-subjects and testing condition (swallowing vs. sip-and-spit) and food sample (four levels) as within-subjects' factors. Additionally, a time series emotional analysis for assessing emotional responses to beverages will be applied to automated facial expression data using the Wilcoxon signed-rank test (Crist et al., 2016) if more sensitive analysis are needed to detect differences between groups. Outcome variables will be checked for normal distribution. Note that linear mixed models to analyse the data can be envisaged to have more statistical power to detect actually existing study effects and to lead to less biased results in the case that the intraclass correlation coefficient and the design effect show dependency in the data (Hox, 1998). Statistical analyses will be conducted using SPSS (IBM, SPSS; Version 23.0, Chicago, IL, USA). Descriptive statistics will be presented using Mean ± *SD* for all continuous variables.

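### Study 1 names the 0–10 intensity ratings as a primary outcome but states no group or condition analysis of them, although a shift common to both samples shows in the ratings and not in the forced choice

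*Protocol article*

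**What the plan says.** **Outcome.** Table 2 has a row, marked primary for Study 1, that holds both "sweetness and fattiness identity and intensity (score") and the signal detection parameters d′, C and ß. The instrument for the row is an "11-point anchored Likert-type scale (scores from 0 to 10) designed to measure taste perception".

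**Data collection.** In the Procedure section, "participants are required to select the one of two food samples, which represents the specified attribute best". The same section says that the samples of each pair "are judged in terms of taste identity and intensity". Table 3 lists the pairs for each of the spit and swallow conditions: "A vs. B, A vs. C, A vs. D, B vs. C, B vs. D, C vs. D".

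**Analysis.** In Data processing, "three direct measures will be derived from the response data of the 2AFC procedure using the SDT". Planned analysis then says that "comparisons of multiples d′s among groups across two testing conditions will be performed for sweetness, creaminess and caloric content scores", and that "confidence intervals, hypothesis tests and multiple comparisons for C and ß will be constructed". The ANOVA on self-ratings, and the remark that linear mixed models could be considered, both stand in the Study 2 paragraph. That ANOVA names hedonic and familiarity ratings, not sweetness or fattiness intensity.

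**The concern.** A primary outcome of Study 1 is collected but has no stated inferential analysis. This is more than condensation for a journal. The article fixes the Study 1 analysis down to spreadsheet formulas and named variance methods, and the intensity ratings are not clearly among the variables tested.

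H1 has two parts: sensory performance should be similar across groups, and currently ill patients should show more response bias, more so when swallowing. The section on expected results describes the bias as a readiness to say that a weight-related attribute is present. Data processing likewise reads C as a tendency that applies across all samples. A tendency to report everything as sweeter or fatter is a shift in level. A forced choice between two samples responds to the difference between them and not to their common level. If the ratings are left out of the inference, the bias part of H1 rests on data that cannot show such a shift. Choosing after the fact between ratings and signal detection measures would also be open.

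**Working it through.** The article gives no figure for this point to reproduce. Its sample size per study (80, with 15 in each currently ill and each control group) enters below only as a group size.

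**1. Common shift, from the article's own definitions.** Let X_H and X_L be the perceived intensities of the higher and lower sample of a pair. The participant picks the higher one when X_H > X_L. Add the same shift s to both: X_H + s > X_L + s exactly when X_H > X_L, so every choice is unchanged. The hit rate H and false alarm rate F computed from those choices are then unchanged, and so are
- d′ = [z(H) − z(F)]/√2,
- C = −[z(H) + z(F)]/2,
- ß = exp{[z(F)² − z(H)²]/2}.

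The mean rating of the pair moves by s, apart from rounding and the ends of the scale. This step needs no assumed variance.

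**2. Simulated size of step 1.** Assumptions: 15 per group; four informative pairs (of the six in Table 3, four differ in sweetness and four in fat); sensory noise SD 1 per sample; between-person SD 0.3; d′ = 2 in both groups; ratings rounded and held within 0–10; two-sided t-test at 0.05; 2,000 runs. For a shift of 0.6 noise SDs in one group, the rejection rate was
- proportion of correct choices: 0.05 (no power),
- within-pair rating difference: 0.05 (no power, as expected),
- mean rating: 0.88.

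**3. Information on the sensory difference.** With X_H ~ N(d′, 1) and X_L ~ N(0, 1), the difference has mean d′ and variance 2. Put m = d′/√2. The standardised rating difference carries information 1 on m per pair. A choice that is correct with probability p = Φ(m) carries φ(m)²/[p(1 − p)].

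Example, d′ = 2: m = 1.414, φ(m) = 0.1468, p = 0.921; 0.1468²/(0.921 × 0.079) ≈ 0.30, so about 70% is lost.

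| d′ | p correct | kept | lost |
|---|---|---|---|
| 0 | 0.500 | 0.637 | 36% |
| 1 | 0.760 | 0.530 | 47% |
| 1.14 | 0.79 | 0.50 | 50% |
| 2 | 0.921 | 0.297 | 70% |
| 3 | 0.983 | 0.106 | 89% |

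**4. Power for a group difference of 0.8 in d′**, same simulation settings as step 2:

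| d′ in the two groups | proportion correct | rating difference |
|---|---|---|
| 0 and 0.8 | 0.60 | 0.77 |
| 1 and 1.8 | 0.48 | 0.76 |
| 2 and 2.8 | 0.25 | 0.77 |

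**5. Sensitivity to the assumptions.** Other simulations used the Table 6 pilot gaps, carried from the 1–7 to the 0–10 scale. The sweetness gaps are 3.21, 3.50, 2.46 and 2.75, mean 11.92/4 = 2.98. With assumed SDs of 1 to 2 points, the gain in power from using ratings ran from about 3 to about 40 percentage points, depending on how the spread and the effect were set. For creaminess, where the mean gap is smaller (2.44), two settings with 15 per group gave gains of only about 4 points (0.17 against 0.13, and 0.19 against 0.14). The direction is stable and the size is not.

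**The case against.** **The signal detection measures fit the hypothesis.** H1 is worded in terms of sensory performance and response bias in a discrimination test, and the article chose signal detection theory to separate the two. Raw ratings mix perception with scale use. This stands: using d′, C and ß is not an error, and the ratings should not replace them.

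**The plan already assigns over-reporting to C and ß.** It does, but by step 1 neither can respond to a shift common to both samples when computed from the choice as the Procedure section defines it. The objection would succeed only if hits and false alarms came from some other response, such as a yes/no judgement, and the article does not say so.

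**A reader might infer that the ratings are cut into correct or incorrect, and that most of their information is discarded.** The documents do not support this. Nothing says that choices are made from ratings. Means and SDs are promised for all continuous variables. The mention of scores in the d′ comparisons leaves open how ratings might enter, and it names creaminess and caloric content where Table 2 names fattiness. Also, more than half of the information is lost only if d′ exceeds about 1.14. The article expects a high d′, which points towards the larger losses, but it gives no number.

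**The power figures for discrimination concern the part of H1 where no difference is predicted.** This is true, so they are secondary. They still bear on how much a finding of similar d′ in groups of 10 to 15 can show.

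**A condensed article may leave a model to a fuller plan.** This would excuse missing detail. It does not excuse an analysis section that is specific for three of the measures in a primary row and silent on the ratings in the same row.

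**Conclusion.** The point holds in limited form. The 0–10 sweetness and fattiness ratings are primary for Study 1 and have no stated group or condition analysis. A common upward shift in perceived or reported intensity leaves the forced choices unchanged, so over-reporting of that kind cannot be detected from them but can be seen in the ratings. That conclusion follows from the article's definitions alone.

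The sizes rest on assumptions. The power of 0.88 for the mean rating depends on the assumed between-person SD of 0.3 and would fall with wider differences in scale use. The loss of 36% at d′ = 0, 50% at 1.14 and 70% at 2 assumes equal-variance normal perception. No single power gain can be claimed for this study.

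**What to change.** Add to the Study 1 paragraph of Planned analysis, alongside d′, C and ß: the 0–10 sweetness and fattiness ratings will each be analysed with a linear mixed model with group, condition (swallow or spit), sweetness level, fat level and their interactions, and random participant effects. The group × level terms address discrimination. The group and group × condition shifts in level address over-reporting.

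State in advance how the models and the signal detection measures together bear on H1, and use the same attribute names in Table 2 and Planned analysis. If no inference on the ratings is intended, remove their primary label instead. That is tidier on paper but leaves the common shift untested.

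The cost is one additional model form on data already collected, with no change to the sessions. The level shift must be reported as reporting or scale use, not as sensitivity.
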